## 10.1.2 Pharmaceutical Form

Clear colourless aqueous solution for infusion

## 10.1.3 Nature and Content of Container(s)

Polyethylene plastic bottle (Ecoflac plus®), 500 ml

Ready-to-use container for single use only. The Investigational Products should be administered immediately after connecting the container to the giving set.

## 10.2 Posology and Method of Administration

### 10.2.1 Dosage

Administration of Investigational Test and Reference Products will be performed as an “add on” fluid administration to a continuous basal crystalloid infusion.

The continuous basal infusion of the crystalloid will be 4 ml/kg bodyweight/h. A balanced crystalloid will be used for basal infusion (Sterofundin ISO).

The “add on” fluid administration of the Investigational Products i. e. of either HES 10%, HES 6% or crystalloid in a blinded manner with boluses of 250 ml will individually be controlled by measuring stroke volume with oesophageal Doppler to achieve a target controlled preload optimum. A detailed algorithm (flow diagram) will provide basis for amount of volume replacement (see also appendix 6)

[figure not shown]

If during surgery an acute haemodynamic deterioration occurs, indicated by an increase in heart rate and a concomitant drop in arterial blood or central venous pressure (as it might occur due to a surgical cause of bleeding) then the re-evaluation

of the Doppler signal has to be performed earlier than after 15 minutes to prevent systemic hypoperfusion.

In case intra-operative volume requirements exceed the amount of bottles of Investigational Product supplied by the pharmacy in a blinded manner then open-label treatment with a balanced crystalloid solution (Sterofundin ISO) will be performed during surgery (also using oesophageal Doppler measurements for deciding on the administration of the fluids).

### **10.2.2 Method of Administration**

The administration of the Investigational Products is performed intravenously. Do not mix with other medicinal products.

### **10.2.3 Duration of treatment**

Treatment with Investigational Product starts after reliable basal oesophageal Doppler measurements are obtained and before skin incision.

After final positioning of the patient in the operating theatre the oesophageal probe will be placed and basal measurements will be recorded after correct placement of probe and reliable measures are obtained. Thereafter, before skin incision, the first bolus of Investigational Product of 250 ml/5 min will be given and the algorithm of the individualized volume replacement therapy is initiated. Oesophageal Doppler guided volume replacement will be performed throughout surgery.

Treatment with Investigational Product ends with surgery when the oesophageal probe is withdrawn. In case all bottles of Investigational Product as compiled by the pharmacist are used up before end of surgery then open-label treatment (in addition to basal balanced crystalloid infusion) with a balanced crystalloid (Sterofundin ISO) will be performed from then on during surgery.

After surgery, on ICU, volume replacement will be performed at the discretion of the attending physician. In case colloidal volume replacement is required on ICU on the day of surgery no HES-product but other colloidal volume replacement (e. g. gelatine) will be used. All volume/fluid replacement therapy will be recorded (separately for colloids and crystalloids).

(Note: The loading of the epidural catheter and start of continuous epidural analgesia will be performed at the end of surgery after all intraoperative, study-related measurements have been finalized.)

## **10.3 Labelling**

The label will be designed in accordance with GMP annex 13 and will contain the information as required by the pertinent national requirements.

See below example for label on the primary container.

As the Investigational Products will be supplied as bulkware to the hospital's pharmacy the secondary label of the respective cartons will only indicate the sponsor's name B. Braun Melsungen AG and the content (i. e. the respective product Tetraspan 10%, Tetraspan 6% or Sterofundin ISO) with batch number and expiry date and the amount of bottles in the carton.

|                                                                                                                                                                                                                                                                                                                                                                                                                                                                                                                                                  |                                                                                                                                                                                                                                                                                                                                                                                                                                                                                                                                                                                                                                                                                                          |
|--------------------------------------------------------------------------------------------------------------------------------------------------------------------------------------------------------------------------------------------------------------------------------------------------------------------------------------------------------------------------------------------------------------------------------------------------------------------------------------------------------------------------------------------------|----------------------------------------------------------------------------------------------------------------------------------------------------------------------------------------------------------------------------------------------------------------------------------------------------------------------------------------------------------------------------------------------------------------------------------------------------------------------------------------------------------------------------------------------------------------------------------------------------------------------------------------------------------------------------------------------------------|
| 
Nur zur klinischen Prüfung bestimmt
 
Studien-Nr.:
 HC-G-H-0803
 EudraCT-Nr.:
 2008-004175-22
 
balanziertes
 Volumenersatzmittel
 (kolloidal oder kristalloid)
 
500 ml Infusionslösung
 zur intravenösen Anwendung
 
Random Nr.
  _ _ _ _ _ _ _ _ 
 
Flaschen-Nr.
  _ _ _ _ _ _ _ _ 
 
Flaschen nur in
 aufsteigender Reihenfolge
 verwenden!
 
Gesamtzahl der Flaschen für
 diesen Patienten
  _ _ _ _ _ _ _ _ 
 
Hauptprüfarzt:
 | 
Anwendung und
 Dosierung
 gemäß Studienprotokoll
 
Nur verwenden wenn die Lösung
 klar und frei von Partikeln und die
 Verpackung nicht beschädigt ist.
 Nach Öffnen der Primär-
 verpackung sofort verwenden
 Zur einmaligen Anwendung;
 etwaige Reste verwerfen
 Nicht über 25°C lagern, nicht im
 Kühlschrank lagern und nicht
 einfrieren.
 Flasche nach der Behandlung
 aufbewahren, und zur
 Zentrumsapotheke zurückschicken.
 
Code Nummer:
 
Verwendbar bis MM/YYYY
 
Ident.-Nr.:
 
B   BRAUN
 B. Braun Melsungen AG
 [name]
 [name]
 [contact]
 |

## 10.4 Packaging

The hospital's pharmacy will be supplied with bulk ware of the Investigational Products with labels of the primary container as stated above. This will enable the pharmacist to compile individual amounts (units/bottles) of Investigational Products as described in detail in section 9.5.

### 10.4.1 Storage

The Investigational Products will be stored separately in the hospital's pharmacy. The pharmacy will supply the Investigational Products in time as requested by the investigator and according to randomisation and blinding procedures (see section 9.5).

Do not freeze, do not store in refrigerator, do not store above 25°C.

### 10.4.2 Investigational Product Accountability

In accordance with regulations, the pharmacist or other appropriate individual, who is designated by the Investigator, will keep an inventory of all clinical trial material (CTM) received. All used and unused CTM must be accounted for on an Inventory Form which will be provided to the pharmacist by the Site Monitor (appendix 7). CTM inventory forms will be examined and reconciled by the Investigator at the end of the study.

These records should include dates, quantities, batch / serial numbers, expiration dates (if applicable), and - if applicable - the unique code numbers assigned to the Investigational Product(s) and study patients. Investigators should maintain records that document adequately that the patients were provided the doses / treatments specified by the protocol.

At the end of surgery all bottles i. e. used (empty or with remainder) as well as unused/unopened bottles which have been compiled by the pharmacist for the individual patient must be returned to the pharmacist for product accountability.

A copy of the completed Inventory Form must be retained in the Investigator's Site File, and a copy must be filed in the Sponsor Trial Master File.

## **10.5 Destruction / Retrieval of Surplus Investigational Products**

Surplus Investigational Products are to be returned to the Sponsor after termination of the entire study. The Sponsor is responsible for the destruction of unused Investigational Products.

## **11 CONCOMITANT THERAPY**

Preoperative medication (e. g.  $\beta$ -blockers, statins, ACE-I, antidiabetics) will be documented on the CRF.

Duration of preop fasting time is standardized (solid food on demand of the attending surgeon, clear fluids up to 2 hours preop) and will be documented in the CRF. Furthermore, type of bowel preparation will be documented in the CRF.

Preoperative medication will be continued on the day of surgery with the exception of subcutaneous rapid-onset insulin, metformin, acetylsalicylic acid and MAO monoamine oxidase)-inhibitors.

Anaesthetic technique will follow a standardized protocol and usually is based on a volatile anaesthetic using desflurane.

Epidural analgesia using ropivacaine 0.2% and sufentanil (concentration will be left to the standard operating procedures of the study centres) 1 mcg/mL will be started at the end of surgery after all study measurements have been completed.

### **Necessary concomitant medication during anaesthesia and pancreatic surgery:**

- Basal balanced crystalloid (Sterofundin ISO) infusion of 4 ml/kg BW/h.
- Inotropic drugs (e. g. noradrenalin, dobutamin, adrenalin, orciprenalin, atropine, enoximone, cafedrin-theodrenalin, levosimendan) will be applied when required and as deemed necessary by the treating physician.
- Administration of sodium bicarbonate 8.4% if pH<7.25 and/or base excess>-10 mmol/l
- Transfusion of erythrocyte concentrate (EC): Trigger is an haematocrit of < 25%. In case severe bleeding occurs EC and fresh frozen plasma (FFP) may be given independently from trigger according to the physician's judgement.
- It is aimed at to transfuse fresh frozen plasma (FFP): following a proportion of EC:FFP = 2:1 for the first 4 infusions of EC; after 4 infusions of EC the proportion is 1:1.
- Infusion of platelet concentrate when thrombocyte count is < 50,000/  $\mu$ l

- If volume requirement during surgery exceeds the amount of Investigational Product compiled then open label fluid replacement with a balanced crystalloid (Sterofundin ISO) is performed.

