|  | 
SAP, DAP, MAP, HR, CVP; PiCCO and oesophageal Doppler: CI, SV, SVR
 
 
○ every 60 min after start of surgery: ITBVI, EVLWI (PiCCO)
 
 
 
▪ Infusion of the investigational Products according to algorithm
 
▪ Hourly blood sampling for intraoperative laboratory evaluation*
 
▪ Diuresis/urinary output (cumulative every 60 min)
 
▪ Concomitant medication and therapy (including inotropic drugs, sodium bicarbonate, infusion of blood products (RBC, FFP, PC) according to the triggers
 
▪ Adverse events and adverse reactions
 
 
*laboratory measurements in blood samples:
 
 
○ 1 hour after start of surgery: haemostasis/coagulation (ROTEM only), blood gas analysis/arterial blood sample (pCO2, pO2, HCO3, SaO2) including acid base status (pH, BE, lactate, bicarbonate) and electrolytes (Na, K, Ca, Cl)
 
○ at 2 hours after start of surgery and then every 60 min intraoperatively: blood gas analysis/arterial blood sample (pCO2, pO2, HCO3, SaO2) including acid base status (pH, BE, lactate, bicarbonate) and electrolytes (Na, K, Ca, Cl).
 
○ blood sampling for BGA should be performed as close as possible to the time, at which the corresponding hemodynamic measurement is done. i.e. ITBVI and EVLWI.
 
 
day 0/ at the end of surgery:
 
 
▪ Haemodynamics (SAP, DAP, MAP, HR, CVP; PiCCO and oesophageal Doppler: CI, SV, SVR; PiCCO: ITBVI, EVLWI)
 
▪ intraabdominal pressure (still in operating theatre directly before extubation)
 
▪ Concomitant medication and therapy, blood products
 
▪ Blood sampling for laboratory evaluation*
 
▪ Investigational Products
 
▪ Diuresis/urinary output
 
▪ Adverse events and adverse reactions
 
 
* laboratory measurements in blood sample:
 
 
○ arterial blood gas analysis (pCO2, pO2, HCO3, SaO2) including acid base status (pH, BE, lactate, bicarbonate) and electrolytes (Na, K, Ca, Cl). Blood sampling for BGA should be performed as close as possible to the time, at which the corresponding hemodynamic measurement is done.
 
○ haemostasis/coagulation parameters (PT, aPTT, Fibrinogen, FVIII:c, vWF-Ag, vWF-RiCo; CT, CFT, MCF using ExTEM und FibTEM)
 
○ cardiac function (Troponin or high-sensitivity Troponin, NT-Pro-BNP)
 
○ inflammatory reaction parameters (facultative: IL-6, IL-10)
 
 |

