#### Blood gas analysis and acid-base status, electrolytes

- pCO2, pO2, HCO3, SaO2
- pH, base excess, bicarbonate, lactate
- sodium, potassium, ionized calcium, chloride

Blood will be sampled as close as possible to the time, at which the corresponding hemodynamic measurement is performed. Measurements will be at

- baseline: arterial blood sample
- intraoperatively (every 60 minutes), arterial blood sample
- postoperative (at the end of surgery): arterial blood sample
- on ICU (including postoperative day 1) on admission, 6 hours after admission, on POD 1 every 6 hours venous or arterial blood gas sample

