## Baseline laboratory

- arterial blood gas analysis (pCO2, pO2, HCO3, SaO2) including acid base status (pH, BE, lactate, bicarbonate) and electrolytes (Na, K, Ca, Cl). Blood sampling for BGA should be performed as close as possible to the time, at which the corresponding hemodynamic measurement is done.
- renal function parameters (*urine*: creatinine,  $\alpha$ 1-MG,  $\beta$ -NAG; *serum*: creatinine, BUN, HbA1c)
- haemostasis and coagulation parameter (PT, aPTT, Fibrinogen, vWF-Ag, vWF-RiCo, F VIII:c; CT, CFT, MCF using ExTEM und FibTEM)
- Inflammamatory parameters (IL6 (facultative), IL 10 (facultative), PCT, CRP, white blood cell count (WBC))
- cardiac function parameters (Troponin or high-sensitivity Troponin, NT-Pro-BNP)

**day 0/** after baseline recordings:

- First bolus (250 mLs/5 min) of Investigational Products
- Start of volume replacement algorithm according to oesophageal Doppler measurements
- Thereafter: start of surgery/skin incision
- Adverse events and adverse reactions

**day 0/** during surgery (after start of skin incision):

- Haemodynamics
  - every 15 min within dosing algorithm cycle when there is no volume optimisation, or 15 minutes after stroke volume optimisation: SAP, DAP, MAP, HR, CVP; PiCCO and oesophageal Doppler: CI, SV, SVR
  - every 60 min after start of surgery: ITBVI, EVLWI (PiCCO)
- Infusion of the Investigational Products according to algorithm
- Hourly blood sampling for intraoperative laboratory evaluation\*
- Diuresis/urinary output (cumulative every 60 min)
- Concomitant medication and therapy (including inotropic drugs, sodium bicarbonate, infusion of blood products (RBC, FFP, platelets) according to the triggers
- Adverse events and adverse reactions

\*laboratory measurements in blood/serum samples:

- 1 hour after start of surgery: haemostasis/ coagulation (ROTEM only), arterial blood gas analysis (pCO2, pO2, HCO3, SaO2) including acid base status (pH, BE, lactate, bicarbonate) and electrolytes (Na, K, Ca, Cl)
- at 2 hours after start of surgery and then every 60 min intraoperatively: arterial blood gas analysis (pCO2, pO2, HCO3, SaO2) including acid base status (pH, BE, lactate, bicarbonate) and electrolytes (Na, K, Ca, Cl)

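### Section 11 prints the base-excess limb of the sodium bicarbonate trigger with the inequality reversed

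*Protocol*

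**What the plan says.** The trigger appears in Protocol section 11 (Concomitant Therapy), in the list headed "Necessary concomitant medication during anaesthesia and pancreatic surgery". The bullet reads "Administration of sodium bicarbonate 8.4% if pH<7.25 and/or base excess>-10 mmol/l". It states no dose, rate or repeat rule.

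Sodium bicarbonate is named in two other places, both describing the period during surgery on day 0:

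- Section 14.1: "Concomitant medication and therapy (including inotropic drugs, sodium bicarbonate, infusion of blood products (RBC, FFP, platelets) according to the triggers".
- Synopsis, visit schedule: "Concomitant medication and therapy (including inotropic drugs, sodium bicarbonate, infusion of blood products (RBC, FFP, PC) according to the triggers".

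Neither gives a pH or base-excess value. The closing reference to triggers there may belong only to the blood products.

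The inotrope bullet in the same section 11 list is explicitly discretionary: those drugs "will be applied when required and as deemed necessary by the treating physician". The bicarbonate bullet has no such wording.

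Section 12.2 lists "pH, base excess, bicarbonate, lactate" and the electrolytes, including sodium, among the secondary safety variables.

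**The concern.** The two limbs of the trigger point in opposite directions. A pH below 7.25 is acidosis. A base excess above -10 mmol/l covers mild deficits, normal values and positive values, which is almost every patient without a severe metabolic acidosis. The base-excess limb therefore takes in the patients who do not need bicarbonate and leaves out those who do.

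Three things are at stake, none of them in the primary analysis.

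- **Treatment.** This is an operative instruction for a concentrated solution, and as written it is wrong.
- **Safety data.** Bicarbonate directly changes pH, base excess, bicarbonate and sodium, all of which the trial measures and compares descriptively. Acid-base behaviour also matters to the product rationale: section 4 presents the balanced formulation as a way to limit acidosis and hyperchloraemia.
- **Compliance.** A site that treats sensibly departs from the written rule. Failure to comply with the protocol is a possible reason for withdrawing a patient (section 9.4.3), repeated non-adherence is a reason for closing a site (section 9.4.2), and a severe protocol violation removes a patient from the per-protocol set (section 16.8). A monitor checking blood gases against section 11 would be using a reversed criterion.

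**Working it through.** No sample size, power or error rate depends on this bullet, so the check is a logical one.

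**Inputs.** The printed trigger comes from section 11. The sodium content of the Tetraspan products (140 mmol/l) comes from section 10.1.1. The intended direction is inferred from the pH limb and from the fact that base excess falls as metabolic acidosis worsens.

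**Rules compared, with and/or read inclusively**

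- Printed: pH < 7.25 or base excess > -10
- Intended: pH < 7.25 or base excess < -10

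| pH | Base excess (mmol/l) | Printed rule | Intended rule |
|---|---|---|---|
| 7.40 | 0 | met | not met |
| 7.35 | -9.9 | met | not met |
| 7.28 | -12 | not met | met |
| 7.25 | -10 | not met | not met |
| 7.20 | -12 | met | met |
| 7.20 | -5 | met | met |

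The pattern is general. When pH is 7.25 or higher the pH limb is off, so the instruction rests on base excess alone, and > -10 and < -10 are opposites except at exactly -10. When pH is below 7.25 the pH limb decides and the two rules agree.

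A grid with pH from 7.10 to 7.55 in steps of 0.01 and base excess from -20 to +10 in steps of 1 confirms this:

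- pH 7.25 to 7.55 is 31 values, and base excess without -10 is 30 values. The rules disagree at all 31 × 30 = 930 points.
- They agree at every point with pH below 7.25.

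These are hypothetical pairs, not patients. They show the reach of the reversal, not how often it would occur.

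**Strict and**

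- Printed (pH < 7.25 and base excess > -10): 7.20 / -12 is not met; 7.20 / -5 is met.
- Sign corrected (pH < 7.25 and base excess < -10): 7.20 / -12 is met; 7.20 / -5 is not met.

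Under this reading 7.40 / 0 does not trigger. The case at 7.28 / -12 does not trigger with either sign, so it no longer separates the two. The printed sign is still wrong, because it withholds bicarbonate from the more severe metabolic acidosis and allows it in the milder one.

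**Strength of the drug.** 8.4% is 84 g/l. With a molar mass of 84.0 g/mol, 84 / 84.0 = 1 mol/l, or 1000 mmol/l sodium, and 1000 / 140 = 7.1 times the concentration in either Tetraspan product. The bullet states no dose, so this describes the solution and not any patient's exposure.

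**The case against.** The case on the other side accepts that the sign is wrong and disputes how much it matters. The bullet is probably loose shorthand for a base deficit beyond -10, and no anaesthetist would give 8.4% bicarbonate at pH 7.40 and base excess 0. With no dose stated, clinical judgement is unavoidable. The same section's list of unauthorised medication exempts concentrated electrolytes used for individual correction, and bicarbonate is prohibited nowhere, so a patient at 7.28 / -12 is not denied treatment. Blood gases and electrolytes are checked every 60 minutes during surgery, and severe hypernatraemia above 155 mmol/l is a named example of a reason for withdrawal. The example at 7.40 / 0 also depends on reading and/or inclusively. On this view it is an editorial slip.

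Much of that stands. The effect on care is likely to be limited, the grid and the sodium ratio illustrate without measuring harm, and the 7.40 / 0 case does need the inclusive reading, although that is the ordinary one.

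It does not make the text correct. The minus sign is printed, and the neighbouring triggers for haematocrit (< 25%) and platelets (< 50,000/µl) are meant literally, so nothing tells the reader to treat this symbol differently. It also makes a damaged inequality sign in the extracted text unlikely. The allowance for individual corrections leaves the trigger as it is. Relying on every site to override a written threshold in the same way is not a reason to keep it.

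**Conclusion.** The concern holds. The base-excess limb of the bicarbonate trigger in section 11 points the wrong way under either reading of and/or, and no other section supplies a correct threshold. Read inclusively, the printed rule reverses the evident intent for every blood gas with pH 7.25 or higher, apart from a base excess of exactly -10, and matches it for every blood gas with pH below 7.25.

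The conclusion rests on one assumption: that the rule is meant to treat acidosis and the intended cut-off is more negative than -10. The pH limb supports this strongly, but the clinical lead should confirm it.

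Its weight is moderate: it should be fixed. It is a wrong threshold in an operative treatment rule, bearing on secondary safety variables and on how compliance is judged. The same rule applies in all arms, the primary endpoints, sample size and type I error are unaffected, and the protocol offers no basis for estimating how many patients it would touch.

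**What to change.** Once the clinical lead has confirmed the intent, amend the bullet in section 11 so that the trigger is pH < 7.25 and/or base excess < -10 mmol/l, adding in brackets that this means more negative than -10. Notify the sites of the corrected threshold by letter.

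Nothing else needs to change. The synopsis and section 14.1 state no threshold, and bicarbonate use during surgery is already recorded there as concomitant medication. The cost is a one-line amendment and a site letter.
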